## Specific research projects

### Project 1 – Tuakana-teina peer education

This project builds on the model from a previous project [36], which resulted in significant gains in social support/connection, life satisfaction/mana motuhake, and HRQOL helping kaumātua prepare for life transitions [36, 37, 94]. While the model was trialled in that project, the current version is a significantly enhanced model with two elements that make it innovative. Firstly, service providers noted the need to test the model with other providers. Secondly, service providers believed that the model could be more effectively applied to kaumātua with greatest needs rather than generally for life transitions, particularly in the context of research showing that Māori are more likely to have unmet needs for primary health care than non-Māori [120]. Through the co-design process the research team will work with each service provider to identify the key health and social issues particular to their community.

Once these are defined and a resource kit is created to guide kaumātua, a small number of kaumātua (*n* = 4) will be purposively selected from each service provider and will take part in a Tuakana Orientation Programme. This programme includes four workshops that offer suggestions for communication skills ground in Te Ao Māori and practice around being a peer educator with specific details identified elsewhere [37]. They will then serve as tuakana (peer educator/supporter) for six teina (recipient of peer education/support) for a period of 6-months. Tuakana will talk with teina up to six times to understand their needs and empower them to gain access to needed health and social services. A community research serves as a coordinator for the project and is a resource for helping tuakana and teina link to specific services. The community researcher also provides a resource booklet of available services in the community that tuakana share with teina during the conversations.

Five providers will participate in this project. We will attempt to randomly select teina using a list of registered kaumatua from each provider (*n* = 24 per provider) and exclude participants with advance dementia or cognitive impairment and any other health conditions the provider feel would negative impact participants. Figure 2 provides a flow diagram of proposed recruitment and data collection procedures.

**Fig. 2 Fig2:**
[figure not shown]
Planned CONSORT Flow Diagram and Data Collection for Tuakana-Teina Project. Note: Participants not allocated to intervention, lost to follow up and excluded from analysis will be calculated at the conclusion of the intervention

The sample size was determined by a balance of resources and power to determine the optimal design and confirmed with the od.exe software [121]. Twenty tuakana and 120 teina will be recruited in total from the five providers; with all tuakana retained/replaced and 67% of teina retention as occurred in a previous iteration of this model [36] it is expected that at least 20 tuakana and 80 teina will be retained. With the assumption of *p* = .05 and intra-class correlation = .01 (from our previous study) [36], there will be sufficient power (=.80) to identify a medium effect (d = .5) in change over time and a group X time interaction. A medium effect size was chosen given prior research on the impact of elder peer educators on self-rated health and related wellbeing outcomes [122, 123] and our previous research [36].

For specific measures, this project will use a measure of elder abuse adapted from a previous scale [124], housing (two items created for the study; one adapted from the Māori Social Survey) [102], and three items on service use and satisfaction (two created for this study and one from our previous project) [36]. See Additional file 1 for the items created for this study. The project has been prospectively registered with Australia New Zealand Clinical Trial Registry (ACTRN12620000316909); it has also received research ethics approval (HREC2019#81).

To test the objective, a mixed-model regression analysis will be used where the participant responses over the three time periods are nested within individual teina and within providers (i.e., a three-level model). Mean responses for each of the key outcomes will be used as the dependent variables (e.g., HRQOL, life satisfaction, health service utilisation (depression). The model will include the following independent variables: a) within group responses (i.e., responses for three time periods) for change over time; b) intervention received or not to identify intervention effect; and c) random intercepts to account for different teina baseline scores. Co-variates will include any independent variables that differ between the two approach groups at the baseline period. An intent-to-treat analysis will be used for the primary testing. A dose-response model will be considered including number of interactions between tuakana-teina and a rating of conversational quality between the tuakana-teina. Also, it will be examined whether missing data due to loss to follow up can be multiply imputed via chained equations [125].

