#### Research design

The research design for each project is a mixed-methods, pre-test and two post-test, staggered design with 2–3 providers receiving the approach first and then 2–3 receiving it on a delayed basis. A pre-test (baseline) of all participants will be completed. The approach will then be implemented with the first providers. There will then be a follow-up data collection for all participants (post-test 1). The second providers will then implement the approach, which will be followed by a final data collection for all participants (post-test 2). This BAG-approved research design enables a rigorous comparison of the approaches whilst ensuring that all participants receive the approach, which is important to a kaupapa Māori methodology [85], and is also considered a novel, strong, ethical, and pragmatic design for approaches in the health service sector [95]. Discussions regarding the design will be on-going, particularly in relation to implementation, to ensure cultural appropriateness and research integrity are maintained throughout the research. It was decided not to include random assignment of providers to the projects, in order to respect the service providers’ choice in participation and to demonstrate a commitment to co-design. However, providers will be randomly allocated to the first or second groups. Previous research with Māori communities and providers shows that research projects that privilege a research model compared to a service model have significant challenges in administering the research [96]. Our research approach acknowledges those findings and seeks to offer an alternative “gold standard” research design for working with kaumātua and Māori communities.

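### Project 1's stated power of .80 for a d = .5 group x time interaction cannot be obtained from its stated inputs with five randomised providers

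*Protocol article*

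**What the plan says.** The Research design section fixes the unit of allocation: "providers will be randomly allocated to the first or second groups", with two or three providers in each group. The Project 1 section adds that "Five providers will participate in this project", so the split must be 2 v 3.

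The sample-size paragraph (after Figure 2) says "Twenty tuakana and 120 teina will be recruited in total from the five providers". It expects 67% of teina, at least 80, to be retained. It continues "With the assumption of *p* = .05 and intra-class correlation = .01", taking the ICC from the group's earlier study, and concludes that "there will be sufficient power (=.80) to identify a medium effect (d = .5) in change over time and a group X time interaction". The design was "confirmed with the od.exe software".

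The Project 1 analysis paragraph plans a three-level mixed model: three time points within teina within providers, with an indicator for intervention received and random intercepts.

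The power statement does not give the repeat-measure correlation, the sidedness of the test, the level the ICC refers to (provider or tuakana), the df, or whether d is in standard deviations of the outcome or of the change.

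**The concern.** One power figure is attached to two different effects. Change over time is a within-person comparison across all 80 teina. The group x time interaction is the controlled comparison, and it rests on five allocated units. With 2 v 3 providers there are 5 - 2 = 3 df between providers, and on 3 df a test needs a much larger standardised effect for the same power.

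If readers take .80 at face value, a null interaction will look like evidence against a medium effect. Depending on the correlation and the df that are justified, the trial may have had much less chance of detecting such an effect.

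**Working it through.** **Inputs.** From the article: 120 teina recruited and 80 retained (120 x .67 = 80.4); five providers, so 80/5 = 16 each; 2 v 3 providers, so 32 v 48 teina; ICC .01; d = .5; alpha .05. Assumed here: two-sided test, d in outcome SDs, ICC at provider level, equal provider sizes, and r = .5 to .8.

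**1. Trying to reproduce .80 without a correlation.**
- Clustering ignored, 32 v 48: SE = sqrt(1/32 + 1/48) = .228; noncentrality .5/.228 = 2.19; power .58 on 78 df (.59 normal). An even 40/40 split gives .60 (.61 normal).
- All 120 recruited teina, clustering ignored: .77-.78.
- 80 teina with design effect 1 + 15 x .01 = 1.15, individual df: .52.
- The 20 tuakana as the clusters: .53-.55 with 4 teina each, .70-.71 with 6 each.

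None reaches .80.

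**2. Provider as the randomised unit, post-test contrast.** SE = sqrt((.01 + .99/16)(1/2 + 1/3)) = sqrt(.0719 x .8333) = .245. Noncentrality .5/.245 = 2.04. Power is .53 by normal approximation and .30 on 3 df. At ICC .05 it is .22 on 3 df.

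**3. What does give about .80.**
- Change score, r = .7, no clustering: SE = sqrt(2 x .3 x (1/32 + 1/48)) = .177; power .80 on individual df.
- Baseline-adjusted, r = .7, design effect 1.15 included: SE = sqrt((1 - .49) x 1.15 x (1/32 + 1/48)) = .175; power .81 on 77 df. The same SE on 3 df gives .50.
- Three-wave model, ICC .01, constant effect: .825 at r = .6 on 77 df, and .80 at r = .7 on 6 df.

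Each route needs a correlation the article does not state and more than 3 df.

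**4. Power at d = .5, ICC .01, 16 per provider.** The baseline-adjusted column uses the variance formula in step 3. The three-wave columns use generalised least squares with period effects, a constant intervention effect and a stable provider effect. Their noncentralities are 2.66, 3.35 and 4.07 at r = .5, .7 and .8, whichever group has two providers. The 6 df are (5 - 2) x (3 - 1), the provider-by-period df within groups.

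| r | Post-test 1, baseline-adjusted, 3 df | Three waves, 3 df | Three waves, 6 df |
|---|---|---|---|
| .5 | .37 | .45 | .60 |
| .7 | .50 | .62 | .80 |
| .8 | .63 | .77 | .92 |

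The noncentrality required for 80% power is 4.26 on 3 df and 3.37 on 6 df. Detectable effects at 80% power, at r = .5, .7 and .8:
- Baseline-adjusted, 3 df: d = .90, .74 and .62.
- Three waves, 3 df: .5 x 4.26/2.66 = .80, .5 x 4.26/3.35 = .64, .5 x 4.26/4.07 = .52.
- Three waves, 6 df: .5 x 3.37/2.66 = .63, .5 x 3.37/3.35 = .50, .5 x 3.37/4.07 = .41.

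If the provider effect is not fully stable over time (cluster autocorrelation .8), the three-wave figures on 3 df fall to .43, .58 and .72.

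**5. Change over time.** Paired comparison, 80 teina, d = .5 in SDs of the change, clustering ignored: noncentrality .5 x sqrt(80) = 4.47; power .99.

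**The case against.** The strongest reply is that the planned analysis is a repeated-measures model, so a post-test-only figure of .30 understates it. This stands. The three-wave model is the relevant one, and its power depends heavily on r.

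A second reply is that 3 df is a choice. Delayed providers cross over to the intervention, so part of the information is within provider. On 6 df the model gives about .80 at r = .7. This also stands as a possible basis for the claim, but the article states neither that r nor that df.

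Three stronger readings are tempting and should not be adopted:
- **That teina were treated as individually randomised.** The paragraph names an ICC and the planned model has a provider level. About .80 can be reached with the design effect included, so matching it without clustering does not show what was done.
- **That power cannot exceed about .65.** That limit belongs to the baseline-adjusted post-test 1 contrast for r up to .8. The planned model gives .77 at r = .8 even on 3 df.
- **That the .01 cannot be a between-provider ICC because the earlier study had one provider.** The article says only that "service providers noted the need to test the model with other providers". It does not say how many providers took part before, and the earlier report is not at hand.

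**Conclusion.** The point holds for the group x time half of the sentence only. The printed inputs do not yield .80 under any calculation tried, even with clustering ignored. The claim can be rescued only by unstated assumptions: r of about .6-.7 with individual-level or within-provider df, or r above about .8 on 3 df in the three-wave model.

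Over r = .5 to .8 the planned model's power runs from .45 to .77 on 3 df and from about .60 to .92 on 6 df. So .80 is unsupported as stated; it is not shown to be unattainable. These figures assume a two-sided test, d in outcome SDs, a provider-level ICC of .01, 16 retained per provider, and a constant effect with a stable provider component. This is a printed figure that its own inputs do not deliver, so a later analysis plan that merely adds detail would not correct it.

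**What to change.** Rewrite the power sentence of the Project 1 sample-size paragraph:
- Give the power for change over time and for group x time separately.
- For group x time, name the provider as the randomised unit, 2 v 3, with about 16 teina retained in each.
- State the repeat-measure correlation and its source, the sidedness, and the SD in which d is expressed.
- Say which level the .01 ICC refers to, and add a sensitivity range, for example .01-.05.
- State the df basis and justify it for five providers.
- Report the recomputed power at d = .5, or the effect detectable with 80% power, for the planned three-wave model.

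The cost is one paragraph and, most likely, a less favourable stated figure. No extra enrolment or change of design is needed.

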### Project 2 – Mātauranga Tuku Iho (intergenerational knowledge and language in action)

This project will highlight the role of kaumātua as carriers of mātauranga [21]; specifically, utilising cultural knowledge exchange as a driver for physical activity. The innovation of this project is that it provides an avenue to increased intergenerational exchange and physical activity that is consistent with cultural values and community activities. The pursuit of cultural knowledge for perpetuating/improving subsequent generations is a key theme of cultural narratives [126], such as Tāne’s ascension and descension through the 12 heavens to obtain the baskets of knowledge [127]; and then to share that knowledge for the preservation and perpetuation of whakapapa (genealogy). Māori narratives centre on “ako” where a reciprocal relationship of mutual learning and teaching between kaumātua and whānau (especially mokopuna or grandchildren) leads to “māramatanga” (change and insights) [128].

A key element of mātauranga is te reo Māori and the project will include language lessons for kaumātua who are not fluent speakers. This is especially important in the context of a generation of kaumātua who faced assimilation policies and practices and were discouraged from learning te reo and hence have experienced cultural dissonance. Research shows a link between speaking te reo, and cultural continuity, which have positive health outcomes [51, 129] including a positive association with HRQOL [40]. This approach involves teaching te reo Māori within the context of learning and sharing mātauranga such as mihi, whakapapa (genealogy), karakia (prayer), and waiata (songs).

The expectation is that the project will be divided into a series of wānanga (or group meetings) that provide instructional sessions about language, tikanga and physical activities across a range of skill levels. The sessions will be tailored to the needs of kaumātua given their previous experiences and knowledge about the session content. The content of the wānanga will be developed through a co-design process with providers and kaumātua and will be documented upon completion.

After the wānanga kaumātua will be asked to engage with at least one member of their whānau to share mātauranga and speak/share reo while participating in a regular activity (e.g., walk to a sacred place; its importance and imperative to preserve the mātauranga of these sacred places is to pass this knowledge on and share stories/pūrākau) that helps improve physical functioning (e.g., participating in Kaumātua Olympics [fun, semi-competitive activities], Iron Kaumātua [triathalon], or simply starting to walk regularly). The intervention is designed to create individually determined improvements on the targeted outcomes. Figure 3 displays a flow diagram of proposed recruitment and data collection procedures.

**Fig. 3 Fig3:**
[figure not shown]
Planned CONSORT Flow Diagram and Data Collection for Project for Mātauranga Tuku Iho. Note: Participants not allocated to intervention, lost to follow up and excluded from analysis will be calculated at the conclusion of the intervention

The specific measures likely will include quality of intergenerational relationships [130], cultural knowledge [102], cultural identity [40], resilience [131], physical functioning [132, 133], and te reo ability. This project will be registered with the Australia New Zealand Clinical Trial Registry, along with completing the application for research ethics after the co-design phase. The project starts 6 months post the start of the tuakana-teina project (originally was 1 year, but COVID-19 restrictions postponed the start of tuakana-teina).

The sample size of 90 kaumātua and 90 whānau members across six providers (*n* = 15 pairs each) was determined by a balance of resources and power to determine the optimal design and confirmed with NCSS-PASS software [134]. Sixty participant dyads are expected to be retained given the 67% retention rate in our previous research [36]. This sample size is sufficient to detect a small to medium effect size (d = .2, power = .80, *p* = .05) in time from pre-test to final post-test and a small to medium effect (d = .3, power = .80, p = .05) for group X time interaction. The chosen effect size is based on a recent study about the impact of small amounts of physical activity on physical functioning for older people [135]. A similar effect is expected for the other specific variables, particularly cultural knowledge for whānau.

To test the objective, a mixed model analysis will be used where the participant responses over time are nested within individuals and nested within providers (i.e., three-level model). Mean responses for each of the key outcomes will be used as the dependent variables (e.g., HRQOL, life satisfaction, physical functioning, cultural knowledge exchange). The model will include the following independent variables: a) within group responses (i.e., responses for three time periods) for change over time; b) intervention received or not to identify intervention effect; and c) random intercepts to account for different teina baseline scores. Co-variates will include any independent variables that differ between the two approach groups at the baseline period. An intent-to-treat analysis will be used for the primary testing. A dose-response model will be considered including the number of interactions between kaumātua and whānau members, the amount of activity engaged in, and measures of the paired relationship of kaumātua and whānau member (e.g., degree of agreement in cultural exchange). It will be determined whether missing data due to loss to follow up can be multiply imputed via chained equations [125].

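### Project 2's 80% power for d = .3 (group by time) and d = .2 (time) with 60 retained pairs does not hold at ordinary repeat-measure correlations, and the 60 applies an individual retention rate to pairs

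*Protocol article*

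**What the plan says.** All references are to the protocol article.

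- **Project 2, sample size.** The plan is "The sample size of 90 kaumātua and 90 whānau members across six providers", 15 pairs in each. On retention: "Sixty participant dyads are expected to be retained given the 67% retention rate in our previous research". On power: "This sample size is sufficient to detect a small to medium effect size (d = .2, power = .80" at p = .05) from pre-test to final post-test, and "a small to medium effect (d = .3, power = .80, p = .05) for group X time interaction". The calculation is said to have been confirmed in NCSS-PASS. The procedure is not named.
- **Project 2, analysis.** A three-level mixed model is planned, with three waves of responses nested in individuals and individuals in providers, and an indicator for whether the intervention has been received.
- **Research design.** "providers will be randomly allocated to the first or second groups", with "2–3 providers receiving the approach first and then 2–3 receiving it on a delayed basis".
- **Project 1, sample size.** Under the same staggered design, 80 retained teina in five providers are said to give power .80 for d = .5, using "intra-class correlation = .01 (from our previous study"). Retention is described as "67% of teina retention as occurred in a previous iteration of this model", and the reference is the same earlier study that Project 2 cites for its 67%.

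**The concern.** The power statement is a positive numerical claim, so it can be checked. Sixty people split 30 against 30 is a small sample for a between-group effect of .3 SD, and allocation is by provider. Project 1 claims only d = .5 with more people under the same design, and nothing stated for Project 2 explains its better figure. The 60 also takes a rate observed in single participants and applies it to pairs, which are complete only when both members stay.

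If the claim is too optimistic, readers will believe that the trial can detect a small-to-medium effect that it would probably miss, and a null result could be misread as evidence of no effect.

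**Working it through.** **Inputs from the article:** 90 pairs, six providers, 67% retention, 60 pairs retained, d = .3 and d = .2, power .80, p = .05, provider allocation, three waves.

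**Assumptions:** two-sided test; 3 v 3 providers; ICC .01 borrowed from Project 1; total SD 1; r between .5 and .9; no provider-by-time variance (any would lower power).

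**1. The plan's own figures.** Retention: 90 × .67 = 60.3, which reproduces the 60. Power: a plain post-test comparison at d = .3 needs 175 per arm for .80, and 30 per arm gives .21. A two-wave comparison of 30 v 30 without clustering gives .21/.31/.44 (change score) or .26/.36/.48 (baseline-adjusted) at r = .5/.7/.8. The stated .80 does not appear.

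**2. Group by time in the planned three-wave model.** The groups differ in treatment status only at post-test 1. With m people per provider, let a = .01 + (r − .01)/m, e = (1 − r)/m and q = a/(a + e). Then

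SE² = (2/3)(a + e)(1 − q)(1 + 2q)/(1 + q).

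For 60 people (m = 10) at r = .7: a = .079, e = .030, q = .725, SE = .1685. Normal-approximation power is Φ(.3/.1685 − 1.96) = Φ(−.18) = .43. On 4 df (six providers, two groups) the noncentral t gives .28.

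| Group by time, d = .3 | r = .5 | .7 | .8 | .9 | r needed for .80 |
|---|---|---|---|---|---|
| 60 people, SE | .212 | .1685 | .139 | .099 | |
| 60 people, normal | .29 | .43 | .58 | .86 | .88 |
| 60 people, 4 df | .20 | .28 | .38 | .63 | .94 |
| 120 as independent, normal | .51 | .71 | .86 | .99 | .76 |
| 120 as independent, 4 df | .33 | .48 | .63 | .88 | .87 |

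**3. Time, pre-test to final post-test, d = .2.** This is a paired t with SE = √(2(1 − r)/n). For n = 60 at r = .7, SE = .10 and power is .50. Over r = .5/.7/.8/.9 it is .33/.50/.67/.93, and .80 needs r = .85. For n = 120 taken as independent, .80 needs r = .70. If d is already in units of the SD of change, power at n = 60 is .33 whatever r is.

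**4. Comparison with Project 1.** Scaling its claim by sample size alone gives .5 × √(80/60) = .58 for 60 people and .5 × √(80/120) = .41 for 120. Neither is .3. This scaling ignores the difference between five and six providers.

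**5. Retention of pairs.** If both members always stay or leave together, 90 × .67 = 60. If they drop out independently at the same rate, 90 × .67² = 40. With 40 pairs, one member analysed and r = .5/.7/.8, time power is .23/.36/.50. Group-by-time power from the formula in step 2 with m = 40/6 is .21/.31/.42 (normal).

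**6. Detectable group-by-time effect at r = .7.** For 60 people: 2.80 × .1685 = .47 (normal) and 3.76 × .1685 = .63 (4 df). For 120 as independent, with SE .1195: .335 and .45.

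**The case against.** The strongest reply is that the answer turns on an unstated correlation, and that the article is a condensed account whose software output is not shown. That has force on several points.

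- **Both figures can be met.** With 120 people counted as independent and r = .8, the normal approximation gives .86 for group by time, and time is .93. Both members are recruited and responses are nested in individuals, so 120 is a possible analysed number. But pair members are likely to be correlated: a within-pair correlation of .2 or .5 cuts 120 to an effective 120/1.2 = 100 or 120/1.5 = 80. The cited effect size also comes from physical functioning in older people, and cultural knowledge is singled out for whānau. For outcomes specific to one role, n is 60.
- **A repeated-measures ANOVA with f = d/2** and 120 independent people returns at least .80 for both figures once r is about .63. However, f = .15 with two groups and two times means a .6 SD difference in change, not d = .3, and that calculation has no providers or pairs in it.
- **Four df is conservative.** It suits a comparison of provider means. The article does not fix the degrees of freedom, so both versions are shown.
- **Complete pairs are not needed for the main model.** The plan is intention-to-treat and considers multiple imputation, so losing one partner need not remove the other. Relatives doing an activity together will probably not drop out independently.

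A reader might infer more than the article supports: that .80 is unattainable, that r must exceed about .91 (true only of a two-wave comparison, which is not the planned model), that clustering was ignored, or that only 40 pairs will remain. Silence in an article does not show how the calculation was done, and missing inputs are not the fault here. The fault is that the stated result does not follow at ordinary values.

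**Conclusion.** The point holds in this limited form. At r = .5 to .8, 60 people give .29 to .58 power for group by time (.20 to .38 on 4 df) and .33 to .67 for time, against a stated .80 for each. The claim is met only at high correlations, about .88 and .85, or under the favourable assumption of 120 independent people, where about .76 and .70 suffice (.87 for group by time on 4 df). It also fits poorly with Project 1's d = .5 from 80 teina.

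Sixty complete pairs is an upper limit, reached only under fully concordant dropout. About 40 is the independent-dropout value and not a forecast. Both values assume that whānau members are retained at the teina rate.

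The size of the shortfall rests on r, the ICC of .01, no provider-by-time variance and the analysed unit, none of which the article fixes for Project 2.

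**What to change.** Rewrite the Project 2 power paragraph for the planned three-wave, provider-randomised model. State:

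- the assumed repeat-measure correlation and ICC;
- the analysed unit for each main outcome (kaumātua, whānau or both), with a within-pair correlation where both are used;
- 40 to 60 complete pairs, with the dropout assumption behind each end;
- the detectable effect in place of d = .3. As an illustration at r = .7 and ICC .01, this is about .47 (normal approximation) to .63 (4 df) for 60 people, or .335 to .45 if 120 are treated as independent;
- the time effect restated in the same way. At r = .7 the paired t reaches .80 at about d = .28 for 60 people and .20 for 120 as independent.

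The cost is one paragraph and a less favourable stated figure. Enrolment and design do not change. The article says that registration and ethics application for Project 2 follow the co-design phase, so the corrected figures can go into both.

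### The three-level models leave out clustering that the design creates: the shared tuakana in Project 1, and the kaumātua–whānau pair and role in Project 2

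*Protocol article*

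**What the plan says.** **Project 1.** Each of the five providers selects four tuakana. "They will then serve as tuakana (peer educator/supporter) for six teina (recipient of peer education/support) for a period of 6-months". The sample-size paragraph states "Twenty tuakana and 120 teina will be recruited in total from the five providers" and, after attrition, "it is expected that at least 20 tuakana and 80 teina will be retained". It plans with "intra-class correlation = .01 (from our previous study" and does not say whether this is a provider-level or tuakana-level value. The analysis paragraph nests responses "nested within individual teina and within providers (i.e., a three-level model". Its listed terms are time, intervention received or not, random intercepts for teina, and covariates that differ between the two groups at baseline. The number of tuakana–teina contacts and the quality of their conversations enter only a dose-response model that is to be considered.

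**Project 2.** "The sample size of 90 kaumātua and 90 whānau members across six providers", as 15 pairs per provider, with sixty dyads expected to remain. After the wānanga, each kaumātua is to share knowledge and language with at least one whānau member during a regular physical activity. The analysis paragraph says "the participant responses over time are nested within individuals and nested within providers (i.e., three-level model". Its terms repeat those of Project 1, including random intercepts for teina baseline scores. The paired relationship appears only in an optional dose-response model.

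**Common Data analysis section.** This nests repeated measures within teina and teina within intervention group. It leaves specific models to the projects, and the two project sections then give them.

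**The concern.** In Project 1 the tuakana delivers the intervention. If some tuakana are more effective than others, the six teina of one tuakana will resemble each other after delivery more than teina elsewhere in the same provider. A model with only teina and provider intercepts cannot represent that.

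In Project 2 the intended mechanism is joint activity, so correlated change within a pair is plausible. The project also expects different things of the two roles. Its effect size comes from physical functioning in older people, while cultural knowledge is singled out for whānau. A single intervention coefficient with no role term would average these.

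At stake are standard errors that may be too small, a Project 2 estimate that is hard to interpret, and no estimate of how far Project 1 results depend on the individual tuakana. That last point matters because the project exists partly to test the model with other providers.

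**Working it through.** **1. The article's own counts reproduce.** Project 1: 5 × 4 = 20 tuakana; 20 × 6 = 120 teina; 120 × .67 ≈ 80 retained; 80/20 = 4 retained teina per tuakana. Project 2: 6 × 15 = 90 pairs; 90 × .67 ≈ 60 dyads, or 120 people. The stated power of .80 cannot be reproduced for Project 2 because no within-person correlation is given. That is a separate matter and is not relied on here.

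**2. Levels in the design against levels in the model.**

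| | Design | Model |
|---|---|---|
| Project 1 | wave, teina, tuakana, provider | wave, teina, provider |
| Project 2 | wave, person (with role), dyad, provider | wave, person, provider |

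The rule for adding covariates would not bring role in. It admits only variables that differ between the first and delayed groups at baseline, and recruitment in pairs gives both groups the same one-to-one mix of roles.

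**3. Formula.** Let r be the true variance of the intervention estimate divided by the variance that the model reports. For a two-sided .05 test with a normal reference, actual type I error = 2 × [1 − Φ(1.96/√r)].

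**4. Project 1.** Inputs from the article: three waves, five providers (taken as two first and three delayed), four tuakana each, and four retained or six recruited teina per tuakana. Assumptions: provider correlation .01, within-person correlation .4 to .7, and a tuakana effect that adds variance only in waves after delivery. Generalised least squares (GLS) with the planned three-level covariance gives:

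| Tuakana ICC | r | Type I error |
|---|---|---|
| .01 | about 1.02–1.04 | about 5.2–5.4% |
| .05 | about 1.08–1.19 | about 6–7% |
| .10 | about 1.16–1.39 | about 7–9.5% |

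If the tuakana component instead replaces part of the residual variance, with four teina per tuakana, the figures are lower: 5.4% at .05 and 5.8% at .10.

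**5. Project 2, correlated change.** With two people per dyad and partners' changes correlated ρ, r = 1 + (2 − 1)ρ and the effective number is 120/r.

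| ρ (assumed) | r | Effective n | Type I error |
|---|---|---|---|
| .2 | 1.2 | 100 | 7.4% |
| .3 | 1.3 | 92 | 8.6% |
| .5 | 1.5 | 80 | 11.0% |

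GLS for the staggered design agrees closely with this.

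**6. Project 2, stable resemblance only.** Suppose partners share a constant level (correlation .1 to .3) and their changes are unrelated. The person intercepts and within-person contrasts then remove most of the dependence. With within-person correlation .5 to .8, type I error is about 5.0–5.3%.

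**The case against.** **An article may leave random effects to the full plan.** The common section defers to project-specific models, and Project 2 awaits co-design and registration. This carries limited weight. The project sections state the number of levels and list the terms, so the point concerns a structure that is written down.

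**Pooling of the roles is not stated outright.** This stands. The article calls the pairs participant dyads and models participant responses, so one model for both roles is the literal reading. It does not exclude separate models. With separate models each pair contributes one person, no dyad term is needed and nothing is averaged.

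**The only ICC given is .01.** It comes from the earlier study of this peer-education model. If it is a tuakana-level value, the Project 1 effect is negligible (5.2–5.4%). The planning would then use a level that the analysis drops. If it is a provider-level value, tuakana clustering has not been addressed.

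**Stronger readings that a reader might infer, and that the documents do not support:**
- That linked people count as wholly independent. The provider level already links them; what is missing is dependence beyond the provider.
- That a simple design effect gives the Project 1 error. With six teina and an ICC of .10 it is 1 + 5 × .10 = 1.50, or 11%. That formula describes a single cross-sectional mean, whereas the planned effect is largely a within-person contrast over three waves.
- That standard errors are certainly too small in both projects. No tuakana or dyad correlation is reported, and stable resemblance alone does little.
- That the pooled Project 2 estimate describes no population. An average over kaumātua and whānau members is definable, though of limited use when the targets differ.

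**Conclusion.** The concern holds as a gap in the stated model structure of both projects. Its numerical effect is conditional. In Project 1 it ranges from negligible at an ICC of .01 to moderate at .10, and only if a tuakana effect arises after delivery. In Project 2 it matters if partners' changes correlate, which joint activity makes plausible but no figure in the article establishes. All error rates above assume known variance components and a large-sample normal reference. The reference to teina in the Project 2 model is a plain textual error. Whether the roles are pooled or separate is an ambiguity to resolve, since the article does not state pooling as a decision. The change should be made before analysis.

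**What to change.** **Project 2.** State who enters each model. Either fit kaumātua and whānau outcomes separately, with no dyad term, or fit them jointly with role, role-by-intervention and a dyad random effect that also allows correlated change within pairs. A dyad intercept alone captures only stable resemblance. Replace teina by participant.

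**Project 1.** Add a tuakana random effect that applies to waves after delivery, grouped by the assigned tuakana so that a replacement does not alter the grouping. State the level to which the ICC of .01 refers. Bring the common section's nesting of teina within intervention group into line with the provider nesting used in the project section.

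**Cost.** The identifiers follow from recruitment and assignment. Intervals widen slightly: in Project 1, from the variance ratios in step 4, by up to about √1.19 ≈ 1.09 at an ICC of .05. With 20 tuakana the variance component will be imprecise and may be estimated at zero. Separate Project 2 models rest on 60 people per role rather than 120, so the power statement should say which number it used.
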